## Abstract

**Background:**

Chronic ankle instability is associated with long-term neuromuscular deficits involving poor postural control and peroneal muscular impairment. Symptoms of chronic ankle instability hinder engagement in physical activity and undermine the patient’s quality of life. Despite the existence of various treatment modalities, none has conclusively provided evidence of clinical effectiveness in counteracting neuromuscular deficits, such as arthrogenic muscle inhibition of the peroneal longus (PL). Pulse electromagnetic field therapy employed as an adjunct biophysical therapy can potentially improve stability by mitigating peroneal muscle weakness and by activating the peroneal muscle. We postulate that by combining standard care (muscle strengthening, balance training, and range of motion exercise) with pulse electromagnetic field therapy, postural control stability and peroneal muscle weakness will significantly improve.

**Methods:**

This is a prospective, randomized, double-blind, placebo-controlled trial. A total of 48 adults with chronic ankle instability will be recruited and randomly allocated into either the intervention or control groups. The intervention group (*n* = 24) will receive active pulse electromagnetic field therapy and standard exercise training, while the control group (*n* = 24) will receive sham pulse electromagnetic field therapy and standard exercise training for 8 weeks. Primary and secondary outcomes will be evaluated at baseline, week 4, 8 as well as at 3-, 6-, and 12-month follow-up visits.

**Discussion:**

Chronic ankle instability is a common debilitating condition without a curative conservative treatment. Investigating different treatment modalities will be essential for improving rehabilitation outcomes in this clinical population. This study will investigate the effectiveness of pulsed electromagnetic field therapy on the functional and clinical outcomes in the chronic ankle instability population. This trial may demonstrate this non-invasive biophysical therapy to be an effective measure to help patients with CAI.

**Trial registration:**

ClinicalTrials.gov NCT05500885. Registered on August 13, 2022.

## Administrative information

Note: the numbers in curly brackets in this protocol refer to SPIRIT checklist item numbers. The order of the items has been modified to group similar items (see http://www.equator-network.org/reporting-guidelines/spirit-2013-statement-defining-standard-protocol-items-for-clinical-trials/).

## Introduction

### Background and rationale {6a}

Lateral ankle sprain (LAS) is one of the most common musculoskeletal injuries, with reports of 7 ankle sprains per 1000 exposures [1]. LAS is not merely an isolated ligamentous injury to the anterior talofibular ligament or calcaneofibular ligament but involves damage to the adjacent structures such as the peroneal longus (PL), which are one of the main ankle muscles essential for maintaining mediolateral stability [2]. Approximately 60% of individuals who sustained an acute LAS do not seek appropriate medical advice [3], potentially exacerbating the development of chronic ankle instability (CAI). CAI currently affects up to 40% of all individuals who have sustained one LAS, and the overall prevalence of CAI is reported to be 46%, ranging between 9 and 76% [4, 5].

CAI is a debilitating condition characterized by persistent symptoms (> 1 year after the index injury) of pain, swelling, diminished ankle range of motion (DROM), recurrent sprains, impaired function, and muscle weakness [4]. CAI hinders individuals from engaging in physical activity and reduces their overall quality of life [6]. It may also predispose to the development of post-traumatic ankle osteoarthritis leading to permanent dysfunction [7, 8]. Because of its high incidence, CAI is a social-economic and health burden estimated to cost ~ USD $11 billion annually, up from 38.2% since 2000 [9].

Muscle strengthening, balance training, and range of motion exercise remain the core tenets of standard care (SC) for CAI. The available evidence that rehabilitative exercise is capable of relieving pain, improving function, and decreasing recurrent ankle sprain is overall superior to a wait-and-see approach; however, the overall effectiveness of SC was low to moderate and inconsistent [10, 11]. A recent review has highlighted that the lone muscle strength training regime did not exert any clinical improvement in dynamic balance or self-reported function [12]. Moreover, in a prospective study, supervised balance training did not demonstrate any long-term improvements in muscle strength and dynamic balance among patients with CAI [13]. It has been suggested that 70% of individuals with CAI do not respond well to rehabilitation [14, 15]. Hence, a novel treatment is urgently warranted in addition to the SC. Overall, although universally adopted, the efficacy of SC remains conflicting and there is an ongoing search for novel treatment strategies with which to target the continuum of neuromuscular impairment and disability in patients with CAI.

Pulsed electrical magnetic field (PEMF) therapy is a biophysical therapeutic modality that has been shown to improve muscle regeneration, reduce pain, and attenuate inflammation in various musculoskeletal disorders and aging [16–19]. Preliminary evidence has demonstrated that PEMF therapy can enhance muscle performance, attributed to the activation of type I and IIa muscular fibers, similar to exercise [20]. The mechanism of PEMF therapy involves the activation of the transient receptor potential canonical-1 mediated calcium channel entry and down-stream regulatory factor, peroxisome proliferator-activated receptor-gamma coactivator (PGC-1α) which modulates mitochondrial activities and muscle contraction, respectively [21–23]. Mainly, PGC-1α activates muscle contraction and skeletal muscle fiber transformation through Ca^2+^/calmodulin-dependent protein kinase IV [24].

Furthermore, unlike electrical stimulation therapies where electrical current travels linearly and superficially from one electrode to the other along the surface of the muscle, the magnetic fields penetrate throughout the muscle with little obstruction in all three dimensions within the volume of the coil system wherein the muscle is contained and without the sensation of electric shock caused by the activation of nociceptors [25]. Indeed, PEMF therapy is commonly associated with analgesic effects and does not induce pain [19, 26–29].

To the best of our knowledge, this is the first clinical trial that investigates the effectiveness of PEMF therapy in the short and long term regarding the clinical and functional outcomes of CAI. In this trial, a rigorous double-blind, randomized controlled trial will be conducted to observe the effects of PEMF therapy in addition to the SC on clinical and functional aspects of CAI. The findings of this study will fill the research gap in the efficacy of PEMF therapy for the treatment of CAI.

### Objectives {7}

The primary objective is to investigate the clinical effects of PEMF therapy and SC on the clinical and functional outcomes in the CAI population. We hypothesize that the combination of PEMF therapy and SC will effectively improve the clinical and functional outcomes of patients with CAI.

### Trial design {8}

This is a prospective randomized, double-blind, placebo-controlled trial with two parallel groups and a 1:1 allocation ratio to investigate the treatment effects of PEMF for participants with CAI. All participants will be randomized into an intervention group (*n* = 24, active PEMF and SC) and the control group (*n* = 24, sham PEMF and SC). Researchers will perform all patient-reported outcome measures (PROM), functional, and ultrasonographic outcomes during baseline assessment, 4 weeks, 8 weeks, and follow-up visits on the 3rd month, 6th month, and 1 year after the commencement of the trial. An overview of the study is displayed in Fig. 1.

**Fig. 1 Fig1:**
[figure not shown]
Overview of the study

## Methods: participants, interventions, and outcomes

### Study setting {9}

This study will be conducted at the Sports Performance and Biomechanics Laboratory at the Prince of Wales Hospital teaching hospital, the Chinese University of Hong Kong (CUHK).

### Eligibility criteria {10}

The eligibility criteria will follow the recommendations of the International Ankle Consortium [30].

Inclusion criteria:Age between 18 and 60 years old.A history of at least 1 significant ankle sprain.The initial sprain must have occurred 12 months before the study enrolment, be associated with pain and swelling, and have interrupted at least 1 day of the desired physical activity.A history of the previously injured ankle joint having “given way,” recurrent sprain, and “feelings of instability.”Cumberland Ankle Instability Tool (CAIT) score ≤ 24.In bilateral cases, the ankle with a lower CAIT score will be considered for treatment.

Exclusion criteria:History of major limb injury or surgery.Other concomitant lower extremity pathology (e.g., osteoarthritis).Other muscular, joint, or neurological impairments (e.g., dementia, cerebrovascular accidents) that affect lower limb functions and hinder the participants from completing the assessments.Pregnant or planning for pregnancy.Metal implantation in their body (e.g., pacemakers).

### Who will take informed consent? {26a}

After the eligible participants have been screened based on the inclusion and exclusion criteria, the orthopedic surgeon or the research team will explain the procedure, the benefits, potential risks, and the confidentially of the information and then obtain their signed consent.

### Additional consent provisions for collection and use of participant data and biological specimens {26b}

The written consent form will permit the researchers to collect and analyze the participant data. All data will be kept for a maximum 5 years after publication and destroyed after that time. The collected data will be anonymously published to the public through conferences and scientific papers. This study does not require any use of biological specimens.

## Interventions

### Explanation for the choice of comparators {6b}

Participants will be randomized into either the intervention group involving the active PEMF therapy and SC regime or the control group, receiving a sham exposure from the same PEMF device and SC regime.

### Intervention description {11a}

Participants randomized into the experimental group will be exposed to PEMF therapy employing a BIXEPS device (Quantum TX Pte. Ltd., Singapore) as previously described by Venugobal et al. [19]. Exposure will be given twice a week for 8 weeks for a total of 16 sessions on their affected foot in adjunct with SC. Each treatment session will last for 10 min. The active PEMF therapy does not produce any sensation, facilitating the blinding process. Meanwhile, the control group will receive the SC and the sham treatment from the same PEMF device. A team researcher will operate the PEMF device and monitor any clinical changes during the randomized clinical trial. Each participant will be tagged with a unique radiofrequency identification (RFID) card supplied by Quantum TX Pte. Ltd. using block randomization to assign the treatment group. To mitigate any selection bias, the block size will be concealed from the investigators, and all will be blinded from the subjective assignment.

A team researcher will be responsible for turning on the PEMF machine for all the participants using the RFID cards. A biostatistician not involved in the participant recruitment will oversee the randomization procedure. Both the research team and the biostatistician will remain blinded during the trial. Participants will use the RFID card to complete the treatment without knowledge of group allocation. Side effects will be reported if there are any.

The treatment procedure requires that the participant be seated at 90 degrees on a chair. The solenoids will be adjusted to cover the lower limb. The BIXEPS device is set to low frequency and amplitude fields (1 mT and 50 Hz) to be applied to the affected limb for 10 min. Sham PEMF therapy and SC will be used for the control group. Since the PEMF therapy does not elicit any sensation, both groups are blinded, and the same SC regime will be administered to both groups. Figure 2 depicts how the participants will be situated relative to the BIXEPS device.

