#### Concealment mechanism {16b}

The randomization will be conducted using an online research randomizer by the chief engineer at Quantum TX and the random order of the treatment allocation will only be shared with the biostatistician, a third party based at the CUHK who is not involved in the recruitment process. The randomization will not be disclosed to either the participants or the trial assessors throughout the intervention period. The participants will be randomly assigned to a unique and identical RFID card in which the PEMF or the sham group are randomly allocated to the RFID card. This is to ensure that the participants and the assessors are both blinded to the unique RFID cards containing the treatment types.

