#### Implementation {16c}

The chief engineer of Quantum TX will generate the randomization, and the randomization results will only be shared with the biostatistician at the CUHK. The research team and the orthopedic surgeons will recruit the participants. The Ph.D. student will assist in the assessment and assign the participants to the interventions. At the end of the intervention, the biostatistician will reveal the randomization results to the research team and orthopedic surgeons for statistical analysis.

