### Assignment of interventions: blinding

#### Who will be blinded {17a}

The assessors and orthopedic surgeons will be blinded to the assignment of the interventions. Since the PEMF therapy will not elicit heat or sensation, the participants will also be blinded to the treatment allocation. The randomization results will only be disclosed to the assessors and the orthopedic surgeons after the PEMF intervention has ended.

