### Composition of the data monitoring committee, its role and reporting structure {21a}

The trial steering committee will include orthopedic surgeons, a Ph.D. student, and a biostatistician. The Ph.D. student will participate in the data collection and analysis under the guidance of orthopedic surgeons and biostatisticians. The biostatistician will monitor the data collection and perform interim results. The ethical committee requires no independent data committee. Furthermore, the PEMF treatment imposes little side effects as a conventional treatment for various musculoskeletal disorders. Therefore, it is a low-risk study.

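### The protocol says the biostatistician stays blinded, yet gives that person the allocation list together with the interim, steering and analysis-guidance roles

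*Protocol article*

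**What the plan says.** All references are to the protocol article.

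- **Intervention description {11a}** gives the biostatistician a role in randomization: "A biostatistician not involved in the participant recruitment will oversee the randomization procedure". It then states the blinding: "Both the research team and the biostatistician will remain blinded during the trial".
- **Concealment mechanism {16b}** has the device supplier's chief engineer produce the randomization, and says that "the random order of the treatment allocation will only be shared with the biostatistician, a third party based at the CUHK".
- **Implementation {16c}** repeats that "the randomization results will only be shared with the biostatistician at the CUHK", and adds: "At the end of the intervention, the biostatistician will reveal the randomization results to the research team and orthopedic surgeons for statistical analysis".
- **Who will be blinded {17a}** says: "The assessors and orthopedic surgeons will be blinded to the assignment of the interventions". It adds the participants, does not mention the biostatistician, and releases the allocation to assessors and surgeons once the PEMF course is over.
- **Composition of the data monitoring committee {21a}** says: "The biostatistician will monitor the data collection and perform interim results". It also places a biostatistician on the steering committee and reports that the ethics committee asks for no independent data committee.
- **Data management {19}** has the biostatistician guide the Ph.D. student, who collects, enters and analyses the data.

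**The concern.** A person who receives the allocation order, keeps it while participants are treated and later hands it over is not blinded. Sections {16b} and {16c} describe exactly that for someone whom {11a} calls blinded.

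The list-holder here is also more than a custodian. The role runs the interim, watches over data collection and guides the person who analyses the data. The steering group on which a biostatistician sits meets weekly ({23}), and interim findings are to be shown at local conferences ({31a}). No independent committee stands between the allocation list and these decisions. As the article stands, Statistical methods {20a} leaves some choices to be settled in the light of the data: whether to transform, what remedial measures to take, and which prognostic covariates to use. Guidance on such choices from someone who knows the arms is a possible route to bias. A final report that repeated the {11a} sentence would also describe a safeguard that was not in place.

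**Working it through.** The check is textual. The only arithmetic is the size of the interim.

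**1. Is it one person?** {11a} and {16b} give the same description: a biostatistician who takes no part in recruitment. {16b}, {16c}, {19} and the interim sentence in {21a} all use the definite article. {21a} uses the plural once, and its committee sentence says only that a biostatistician is a member. Nowhere does the article set an unblinded list-holder apart from a blinded trial statistician. One person is the natural reading.

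**2. Could the list be uninformative?** If it held card numbers without arm labels, {11a} might survive. But {16b} speaks of the order of treatment allocation, {16c} has the biostatistician reveal the results to others, and no coding step is described. That reading fails.

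**3. Which sections agree?**

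| Section | Status of the biostatistician |
|---|---|
| {11a} | blinded during the trial |
| {16b} | receives the allocation order |
| {16c} | receives it and later reveals it |
| {17a} | not among those listed as blinded |

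{16b} and {16c} agree with each other, and {17a} is consistent with them. The {11a} sentence stands alone.

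**4. What does the role do while holding the list?** It monitors data collection and performs the interim ({21a}), and it guides data collection, entry and analysis ({19}). The steering seat is in {21a}.

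**5. Size of the interim.** Inputs: 20% of participants having completed 8 weeks of treatment (Interim analyses {21b}) and 48 participants in total (Abstract, Methods). 0.20 × 48 = 9.6, so about 10 participants. The biostatistician would already hold the allocation order at that look.

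**6. When is the allocation released to the others?** {16c} and {17a} release it when the intervention ends. Treatment lasts 8 weeks, and outcomes are assessed up to month 12 (Outcomes {12}). The article does not say whether the end is counted per participant or for the whole trial. If per participant, the assessments at months 3, 6 and 12 follow the release for everyone. If for the whole trial, they still follow it for those treated last.

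**The case against.** The strongest reply accepts the contradiction and disputes its consequences. Much of it stands.

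- **A reader might infer that the protocol promises a blinded analysis and breaks that promise.** The document does not support this. No section says the final analysis is blinded, and {16c} releases the allocation to the team precisely so that it can be analysed. The double-blind label fits the list in {17a}.
- **A reader might infer that every post-baseline outcome is compromised by the biostatistician's list.** This is too strong. The biostatistician is not described as recruiting, treating or measuring anyone. Once the intervention ends, the analysing Ph.D. student would know the arms in any case.
- **The open choices in {20a} may be closed in an analysis plan that is not shown.** That is correct, so it cannot be established that data-dependent choices will in fact be made by someone who knows the arms.
- **The interim is for feasibility and safety, with no efficacy stopping rule stated.** A statistician with allocation access may properly carry out such a look. The problem is that {11a} says this person has no access.
- **Correcting one sentence in {11a} would remove the contradiction.** It would make the text consistent, but the list, the interim and the guidance of the analysis would stay in the same hands.

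None of this reconciles {11a} with {16b} and {16c}. It is also not a matter of detail left to a fuller document, because two printed statements conflict.

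**Conclusion.** The contradiction is real. The article claims that the biostatistician is blinded, while its own allocation sections make that person the only holder of the list at CUHK. The stated blinding therefore does not hold for the interim at about 10 participants, for steering decisions, or for the analysis guided by that role.

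The consequence goes no further than that. No numerical result is affected, and recruitment, treatment delivery and measurement are not directly touched by the biostatistician's access. The conclusion rests on two readings: that the biostatistician is one person throughout, and that the shared list identifies the arms. The text favours both. If the full protocol or analysis plan names a separate blinded statistician, the point reduces to clarifying the article.

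It should be corrected, because the change is cheap and closes an avoidable route to bias.

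**What to change.** **Preferred: make the {11a} sentence true.**

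1. Keep the list with the engineer who already generates it. Lodge a sealed copy with an office independent of the trial team, such as the ethics office, so that a code break does not depend on the device supplier alone.
2. Have the biostatistician and the Ph.D. student work on arms coded A and B until database lock, including at the interim.
3. Amend {16b}, {16c} and {17a} together. If {16c} and {17a} still release the allocation at the end of the intervention, they will contradict coded arms until lock, and follow-up to month 12 will continue after release.
4. In {11a}, limit the biostatistician's oversight of randomization to the procedure, without access to the list.

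**Minimum: if the biostatistician is to keep the list,** say so in {11a}, and have the interim and the analysis choices made by someone who does not hold it.

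**Cost.** The preferred change needs wording in four sections and one sealed file, with no extra staff. Its drawback is that code breaks go through the file holder instead of the biostatistician. The minimum change needs a second person for the interim and the analysis choices.

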**Fig. 2 Fig2:**
[figure not shown]
Demonstration on participant being treated with PEMF therapy

The administered SC exercise regime to the participants will be adapted from Alahmari et al. [31] with a detailed regime made into a booklet for the participants. Participants must conduct a warm-up (stretching around the ankle joint) for 5 min before the exercise regime. Participants will be required to engage between the first and 3rd week; participants will be required to participate in balance training while standing on an unstable surface between the first and third week. The treatment regime consists of 5 times/week for 15 to 20 min a day. During the wobble-board training, participants must move from front to back, left to right side for 15 s, 10 repetitions, with 10 s of rest between each repetition. Participants are later required to move in a circle for 60 s, 5 repetitions, with a rest of 20 s between each repetition.

Between the fourth and eighth week, participants will advance to flexing their knees on the wobble board and repeating the same exercise performed during the first to third week. Each repetition will last for 30 s, with a total of 5 repetitions. A rest period of 20 s will be observed between each repetition. Participants must be in a unilateral stance with eyes opened and closed for 7 s and 4 s, respectively, in sets of 5 with a 10-s rest. Concurrent with the balance training, participants will participate in the ankle muscle strengthening exercise using resistant bands (Thera-bands). Participants are required to sit on the floor with one end of the tubing tied around the treatment table and the other wrapped around the affected foot’s involved metatarsals. Participants will perform different ankle rotations using resistant bands, such as eversion, inversion, plantarflexion, and dorsiflexion. Regardless of the tension of the band, participants are required to stretch the band at 170% of the resting length. Exercise progression will include increasing the number of sets from 1 to 3 for 8 to 10 repetitions each—lastly, stretching of the ankle joint during the cooling session. The major exercise regime can be seen in Fig. 3.

